# Endoscopic vacuum therapy versus stent treatment of esophageal anastomotic leaks (ESOLEAK): study protocol for a prospective randomized phase 2 trial

**DOI:** 10.1186/s13063-021-05315-4

**Published:** 2021-06-02

**Keywords:** Self-expanding metal stents, Endoscopic vacuum therapy, Anastomotic leaks, Esophagectomy, Esophageal cancer, Interventional endoscopy

## Abstract

**Background:**

Intrathoracic anastomotic leaks represent a major complication after Ivor Lewis esophagectomy. There are two promising endoscopic treatment strategies in the case of leaks: the placement of self-expanding metal stents (SEMS) or endoscopic vacuum therapy (EVT). Up to date, there is no prospective data concerning the optimal endoscopic treatment strategy. This is a protocol description for the ESOLEAK trial, which is a first small phase 2 randomized trial evaluating the quality of life after treatment of anastomotic leaks by either SEMS placement or EVT.

**Methods:**

This phase 2 randomized trial will be conducted at two German tertiary medical centers and include a total of 40 patients within 2 years. Adult patients with histologically confirmed esophageal cancer, who have undergone Ivor Lewis esophagectomy and show an esophagogastric anastomotic leak on endoscopy or present with typical clinical signs linked to an anastomotic leak, will be included in our study taking into consideration the exclusion criteria. After endoscopic verification of the anastomotic leak, patients will be randomized in a 1:1 ratio into two treatment groups. The intervention group will receive EVT whereas the control group will be treated with SEMS. The primary endpoint of this study is the subjective quality of life assessed by the patient using a systematic and validated questionnaire (EORTC QLQ C30, EORTC QLQ-OES18 questionnaire). Important secondary endpoints are healing rate, period of hospitalization, treatment-related complications, and overall mortality.

**Discussion:**

The latest meta-analysis comparing implantation of SEMS with EVT in the treatment of esophageal anastomotic leaks suggested a higher success rate for EVT. The ESOLEAK trial is the first study comparing both treatments in a prospective manner. The aim of the trial is to find suitable endpoints for the treatment of anastomotic leaks as well as to enable an adequate sample size calculation and evaluate the feasibility of future interventional trials. Due to the exploratory design of this pilot study, the sample size is too small to answer the question, whether EVT or SEMS implantation represents the superior treatment strategy.

**Trial registration:**

ClinicalTrials.gov NCT03962244. Registered on May 23, 2019.

DRKS-ID DRKS00007941

**Supplementary Information:**

The online version contains supplementary material available at 10.1186/s13063-021-05315-4.

## Background

Intrathoracic anastomotic leaks occur in up to 20% after Ivor Lewis esophagectomy. This complication is associated with a prolonged hospital stay and increased postoperative mortality and therefore one of the most feared complications in visceral surgery [1–4]. During the last years, there has been a controversial debate about the optimal treatment strategy of anastomotic leaks ranging from conservative over interventional endoscopic to surgical approaches [4–6]. While early anastomotic leaks, particularly in the presence of sepsis, as well as extended conduit necrosis still remain a recommended indication for surgical revision, growing expertise suggests endoscopic treatment in the case of leaks, which are defined as localized retentions connected to the site of anastomotic insufficiency [7–10]. The current gold standard in the endoscopic management of anastomotic leaks seems to be the usage of self-expanding metal stents (SEMS), with success rates of approximately 70–81%. Endoscopic vacuum therapy (EVT) represents a newer alternative that has been introduced by Wedemeyer and colleagues in 2008. Since then, an increasing number of patients has been treated with this method showing promising results in retrospective studies: The healing rates range between 67 and 100% [11–18]. Both treatment strategies present advantages and drawbacks: While SEMS provide a complete seal of the leak and maintain the esophageal passage for oral intake, they might induce ischemia and require the placement of additional drainages in some of the patients. Stent migration is a common problem calling for re-interventions. Endoscopic vacuum therapy offers continuous fluid collection facilitating the granulation process and reducing bacterial proliferation, but needs to be changed every 2–5 days, requires a trans-nasal suction drainage, and forbids oral nutrition [19, 20].

A recent systematic review identified five retrospective studies comparing both methods and the meta-analysis of the data suggested that EVT had a higher rate of leakage closure than SEMS [21]. Nevertheless, no clear recommendations can be made due to methodological weaknesses of the underlying retrospective studies. So far, there is no prospective data concerning the optimal endoscopic treatment for anastomotic leaks calling for comparative studies to strengthen the evidence. To our knowledge, the ESOLEAK trial is the first study to compare SEMS and EVT for the treatment of anastomotic leaks after esophagectomy in a prospective, randomized design.

## Methods

### Aim and design of the study

The aim of the open, randomized ESOLEAK study is to investigate in a prospective manner two different endoscopic treatment modalities of anastomotic leakages after Ivor Lewis esophagectomy, namely the endoscopic placement of self-expanding metal stents (SEMS) and the endoscopic vacuum therapy (EVT).

The trial will be conducted as a phase 2 randomized trial at two tertiary medical centers with the aim to define appropriate outcome measures and study population size for a larger interventional trial. The study design is illustrated in Fig. 1.

**Fig. 1 Fig1:**
[figure not shown]
Flow chart illustrating the study design

### Patients

This study will be conducted at the University Hospital of Cologne and the University Medical Center Hamburg-Eppendorf and include a total of 40 patients (n=40). The number of patients is estimated in order to show the feasibility of the trial protocol and to provide data to calculate the sample size for a larger randomized prospective interventional trial.

All patients with resectable esophageal cancer will be screened for eligibility to be enrolled in the study. Informed consent will be obtained preoperatively before the inclusion criterion of an anastomotic leak is satisfied.

#### Inclusion criteria

Histologically confirmed esophageal cancer or similarly operated neoplasiaEsophagectomy with intrathoracic esophagogastric anastomosisEndoscopically diagnosed esophagogastric anastomotic leakClinical signs or symptoms due to the leak or elevated inflammatory parameters, most likely linked to the anastomotic leak≥ 18 years of agePatient’s ability to understand the study extent and consequencesSigned informed consent form

#### Exclusion criteria

Macroscopically incomplete resection of the tumor (R2), palliative resectionEndoscopically verified necrosis or critical ischemia of the conduitSize of the leak larger than 50% of the anastomotic circumferenceImpossibility to place a CT- or ultrasound-guided drainage if evacuation is needed in case of SEMS placementEarly (≤ 48 h postoperative) and late (> 4 weeks postoperative) anastomotic leaksTherapeutic anticoagulationSigns of severe sepsis requiring urgent surgical treatmentPregnancy and lactation

### Randomization

In case of clinical, radiological, or laboratory suspicion of an anastomotic leak after Ivor Lewis esophagectomy, a diagnostic upper gastrointestinal endoscopy will be performed. If an anastomotic leak is verified endoscopically and all inclusion and exclusion criteria are met, patients will be randomly assigned to either control (SEMS) or experimental (EVT) group with a 1:1 allocation using a web-based, centralized permuted block randomization system. The allocation will be final and the researchers will not be able to influence the results. Due to the character of the intervention, a blinding is impossible.

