### Trial intervention

#### Endoscopy

Each diagnostic endoscopy in the course of the study will be performed by a maximum of three experienced endoscopists per center following a standardized protocol and will be described in detail and visually documented in photo and video (Fig. 2). Regardless of the group allocation, irrigation should only be performed in endoscopically accessible cavities. After the allocation to one of the groups, we ensure endoscopic treatment within a period of 12 h after diagnosis by implementing a 24/7 on-call service.

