#### Control group (SEMS)

Stents used in this study must be self-expanding, partially covered metal stents (CE certified - CE0197). The product will be narrowed down to a few models, but the final decision regarding the stent type and size will be left up to the endoscopist. The stent may be secured in its position by using clips or endoscopic suturing techniques. To achieve optimal coverage and seal of the leak, the flare ends of the stent need to be proximal and distal to the leak. In case of stent dislocation or migration, the stent may be repositioned and fixed or replaced by another model or size with better adjustment. This scenario will be documented as a complication. After successful stent placement, a triple lumen nasojejunal feeding tube suitable for intestinal feeding and gastric decompression is inserted. The stent will be removed or replaced after 21 days (±2 days).

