### Follow-up

Following the primary endoscopic intervention, the patient will be treated according to the clinic’s standard operating procedures. If the patient’s clinical status does not improve within 72 h, endoscopic reevaluation and/or another CT scan will be performed. In case of new fluid collections, a drainage will be inserted. If endoscopy shows necrosis or severe ischemia of the interponate or a significant increase of the anastomotic leak size, a surgical revision will be evaluated by the treating physician taking into account the patient’s clinical status.

During the hospital stay, the following data are determined on days 3, 7, 14, 21, and 28 and then weekly (±1 day) after the diagnosis of anastomotic leakage as illustrated in Table 1: vital signs, SOFA score, duration of ventilation, leukocytes, CRP, and procalcitonin value, if applicable [22]. All relevant endoscopic, surgical, and non-surgical complications throughout the hospital stay including postoperative death will be documented in the CRF (Table 1). Follow-up examinations are performed 3 and 6 months (±14 days) after inclusion (Table 1). In addition to assessing the quality of life and the clinical status, the following details are documented on follow-up visits: body weight, Karnofsky index, presence of dysphagia or a symptomatic stenosis, oncologic status (relapse/remission), and tumor-specific therapy, if applicable. The recurrence rate and mortality including the cause of death will be documented beyond the last study visit contacting the treating physician or the patient.

**Table 1 Tab1:** Trial events according to treatment and follow-up plan

		Intervention phase		Follow-up (time after informed consent)		
Trial checkpoint	Screening	Prior to treatment	Hospital stay after inclusion	3 months (± 14 days)	6 months (± 14 days)	12 months (± 14 days)
**Informed consent**	X					
**Inclusion/exclusion criteria**	X					
**Medical history, physical examination, vital signs**	X^a^	X	X^b^	X	X	X
**Diagnostic upper GI endoscopy**		X				
**CT scan**		X	(X)		x	
**ECG**	X					
**Laboratory tests**	X	X	X^b^	X	X	X
**Operative report**		X	X			
**Postoperative complications, treatment failure**		X	X			
**SOFA score**		X	X^b^			
**QoL questionnaire**	X		X^c^	X	X	X
**Treatment costs**			X			
**Monitoring of SAE**		X (from randomization to discharge from hospital + 30 days)				
**Overall survival**		X				

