### Statistical analysis

The primary analysis and the analysis of the secondary endpoints will be conducted according to the intention-to-treat (ITT) principle including all patients. Each patient will be analyzed independent of the group allocation.

To assess the quality of life, either a t-test for independent groups or a Mann-Whitney U test is performed at the two-sided level of 5% depending on the distribution type.

For statistical evaluation of the secondary endpoints, parametric and non-parametric analyses will be conducted depending on the distribution type.

*p*-values < 0.05 are considered statistically relevant, but merely in a descriptive manner. Quantitative variables are described by mean value, standard deviation, and quartiles, and qualitative variables by absolute and relative frequency. The effect size is calculated as follows: With two unrelated samples (*n* = 20), α = 0.05, and power = 0.8, an effect of 0.909 can be calculated.

All comparisons with respect to the targets explicitly mentioned elsewhere are exploratory and therefore differences are considered significant if the respective p-value is less than 0.05. Subgroup analyses regarding, e.g., SOFA scores are planned.

The analysis of the data will be performed as an intention-to-treat analysis. In case of missing data, the effect on the results will be assessed via sensitivity analysis of augmented data sets. Reasons for missing data will be analyzed and qualitatively compared between the two groups.

In advance, all planned analyses will be specified in a statistical analysis plan (SAP), which will be finalized based on pooled data analysis before the first comparative analysis. No interim analysis is planned for this trial.

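### Two centres share 40 patients, but the protocol names no stratification by centre and its quality-of-life test has no centre term.

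*Protocol article*

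**What the plan says.** Under Randomization, the protocol article assigns patients "with a 1:1 allocation using a web-based, centralized permuted block randomization system". Neither that section nor any other names a stratification factor. The abstract says the trial "will be conducted at two German tertiary medical centers and include a total of 40 patients within 2 years"; how the patients divide between the centres is not given.

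Under Follow-up, local practice enters: "Following the primary endoscopic intervention, the patient will be treated according to" the clinic's standard operating procedures. Under Control group (SEMS), "the final decision regarding the stent type and size will be left up to the endoscopist", from a list narrowed to a few models.

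Under Statistical analysis, quality of life is compared by an independent-groups t-test or a Mann-Whitney U test, two-sided at 5%, with no centre term. The section gives the detectable effect as "With two unrelated samples (*n* = 20" per group, "α = 0.05, and power = 0.8, an effect of 0.909 can be calculated". P-values are described as descriptive, and detailed analyses are deferred to a SAP that is not shown. Under Patients and under Duration of study and sample size calculation, one stated purpose is to supply data for sizing a larger trial.

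**The concern.** Centre appears in neither the stated allocation nor the stated test. Length of stay, intensive care time, time to oral intake and quality of life can all depend on how a unit manages recovery and discharge. In a trial of 40, blocks that balance the arms overall can still leave one centre over-represented in one arm. Any difference between centres then sits inside the observed arm difference, and a two-group test cannot separate it.

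The second stake is specific to a pilot. An SD that contains an unmodelled centre difference is larger than the within-centre SD that a centre-adjusted trial would need for its sample size.

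**Working it through.** **Inputs.** From the article: 40 patients, two centres, 1:1 allocation, 20 per arm, two-sided alpha 0.05, power 0.80, detectable effect 0.909. Assumed, because the article gives neither: the centre split (20/20, with 26/14 and 30/10 as alternatives) and the difference between centres, δ = 0.5 to 0.8 within-centre SD.

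**1. The article's own figure.** Two-sample t-test, noncentral t, 38 degrees of freedom, 20 per arm, two-sided 5%, power 0.80: d = 0.9091. The stated 0.909 is reproduced. It comes from a formula without centre.

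**2. Chance of an uneven split, if the list is unstratified.** Let X be the number from one centre (20 patients) who fall in one arm (20 of 40):

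P(X = x) = C(20, x) · C(20, 20 − x) / C(40, 20)

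- P(10) = 0.248; P(9) + P(11) = 0.409
- 12 v 8 or worse: 1 − 0.248 − 0.409 = 0.343
- P(8) + P(12) = 0.230, so 13 v 7 or worse: 0.343 − 0.230 = 0.113

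| Centre split | Off proportional by ≥ 2 patients | By ≥ 3 patients |
|---|---|---|
| 20/20 | 34% | 11% |
| 26/14 | 32% | 10% |
| 30/10 | 27% | 6.5% |

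These figures fix the centre totals and ignore the blocks. Simulating unstratified blocks of 4 with random centre totals (50:50 expected), a gap in centre share of at least 20 points occurs in 26% of trials and of at least 30 points in 7.9%.

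**3. Shift in the observed difference.** Shift = (difference in centre share between arms) × δ.

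- 12 v 8: (12/20 − 8/20) × δ = 0.20δ, or 0.10 to 0.16 SD
- 13 v 7: (13/20 − 7/20) × δ = 0.30δ, or 0.15 to 0.24 SD

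The largest of these is 0.24/0.909 = 26% of the detectable effect. The standard error of the difference is √(2/20) = 0.32 SD.

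**4. Error rate.** Simulated type I error of the unstratified, unadjusted t-test is 0.048, 0.048 and 0.047 at δ = 0, 0.5 and 0.8. Stratifying without a centre term makes the test conservative: 0.033 at δ = 0.8.

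**5. Variance and power.** With equal centres, ignoring centre adds 0.25δ² to a within-centre variance of 1: 0.25 × 0.25 = 0.06, and 0.25 × 0.64 = 0.16. A sample size built on that variance is about 6 to 16% too large for a trial that adjusts for centre. Simulated power at 0.909 SD falls to about 0.78 at δ = 0.5 and 0.75 at δ = 0.8. A repeat run with exactly 20 per centre and unstratified blocks of 4 gave 0.77 and 0.74. With stratification and a centre term, power stays near 0.80.

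**6. After stratifying.** With centre-stratified blocks of 4 (size assumed) and a 50:50 split, the SD of the gap in centre share falls from 0.157 to 0.033. No gap of 20 points or more was seen in 20,000 runs.

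**The case against.** The article is silent on stratification. A reader might infer that it describes a single list not tied to centre, but it does not: centralised says where allocation is run, and such a system can stratify by site. The article condenses a fuller protocol, and a SAP is to follow, so a stratification factor and a centre term may exist there. This stands, and it limits the point to what the article states.

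A reader might also infer that chance imbalance invalidates the comparison or passes off a site difference as a device effect. That is not supported. Unstratified randomisation has zero expected bias and the 5% test keeps its level. Even the 13 v 7 case with δ = 0.8 shifts the estimate by less than one standard error. P-values are descriptive, and the article says the trial is too small to decide superiority.

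Site differences are also limited by common rules: a standardised diagnostic endoscopy protocol, one suction standard, shared drainage and enteral feeding rules, and supportive care by international guidelines. The article does not say that the two clinics' procedures differ. These rules narrow δ but do not show it to be nil.

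In an open trial, blocks run within a site are easier to predict than blocks spread over both sites. That is a real cost of the remedy.

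Finally, the article says "Each diagnostic endoscopy in the course of the study will be performed by a maximum of three experienced endoscopists per center", which might prompt a call to extend that limit to sponge or stent placement. Doing so would not correct a centre imbalance, and it is not part of this point.

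The case for change remains because the one comparison the article fixes takes no account of centre. Also, the variance estimate is a product of this pilot whether or not its p-values are confirmatory.

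**Conclusion.** The point holds as a design improvement, not as an error that invalidates the trial. As stated, neither allocation nor the quality-of-life test uses centre. If the list is unstratified and the centres are equal, a 12 v 8 or worse split has about a 34% chance and 13 v 7 or worse about 11%. At an assumed δ of 0.5 to 0.8 SD, a 13 v 7 split moves the observed difference by 0.15 to 0.24 SD. Ignoring centre costs roughly 2 to 6 points of power at 0.909 SD and inflates the variance handed to the larger trial by about 6 to 16%. There is no average bias and no inflated type I error.

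The sizes rest on the assumed split and centre effect, and the imbalance figures also on the list being unstratified. If the full protocol already stratifies by centre, only the analysis part remains, and it is then needed because the plain test becomes conservative.

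**What to change.** Before recruitment, confirm or set the web system to 1:1 permuted blocks stratified by centre, with varying block sizes not disclosed to the sites, and say so under Randomization. Under Statistical analysis and in the SAP, include centre as a factor in the between-arm comparison of quality of life and the main secondary endpoints, for example a linear model or a centre-stratified Wilcoxon test. Report the within-centre SD for use in sizing the larger trial.

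The two parts belong together, though the centre term alone recovers most of the precision. With unstratified allocation and 20 patients per centre, the SD of the gap in centre share is 0.160. Adjustment then costs on average only about 1/(1 − 0.160²) = 1.026, or 2.6%, in variance.

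The cost is one system setting, one model term and one degree of freedom, a possible incomplete block at each site, and slightly greater predictability of allocation within a site, limited by the varying block sizes. The article gives the status as not yet recruiting, and the allocation scheme cannot be repaired for patients already randomised.

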### Trial intervention

#### Endoscopy

Each diagnostic endoscopy in the course of the study will be performed by a maximum of three experienced endoscopists per center following a standardized protocol and will be described in detail and visually documented in photo and video (Fig. 2). Regardless of the group allocation, irrigation should only be performed in endoscopically accessible cavities. After the allocation to one of the groups, we ensure endoscopic treatment within a period of 12 h after diagnosis by implementing a 24/7 on-call service.

**Fig. 2 Fig2:**
[figure not shown]
Standardized documentation of diagnostic and therapeutic endoscopies

#### Intervention group (EVT)

Before the endoscopic placement of the vacuum therapy system, a triple lumen nasojejunal feeding tube is inserted for gastric decompression and to ensure intestinal feeding throughout the duration of the EVT.

The sponge system can be either positioned inside the esophageal lumen (endoluminal position) or into the extraluminal cavity adjacent to the anastomotic leak (extraluminal position). Anastomotic leaks without an accessible extraluminal cavity will be treated by endoluminal sponge placement whereas anastomotic leaks with larger cavities are treated by inserting a manually customized sponge into the cavity. The sponge system will be placed using an overtube and a pusher. Hereafter, the sponge position will be controlled endoscopically and may be adjusted using a forceps. Then the drainage tube is placed via the nasal cavity and secured with adhesive strips or a nasal tube retaining system (e.g., AMT Bridle™, Applied Medical Technology, USA). Subsequently, the drainage tube will be connected to an electronic vacuum pump with a defined continuous suction (e.g., VivanoTec®, Hartmann AG, Germany). Since there is no data concerning the selection of the ideal suction power for EVT, we decided to use a suction power of 125 mmHg, which we have established as a standard in our center in Cologne and Hamburg since 2010. The system exchange or removal is scheduled 3–5 days after the initial placement. To ensure an atraumatic removal of the sponge system, the drainage tube is disconnected from the vacuum pump and 40 ml of saline solution is injected into the tube to wet the sponge and thus facilitate removal. The EVT may be terminated either after full closure of the leak or complete lining of the cavity with granulation tissue. Dislocation or migration of the sponge system is classified as complications.

